### **4.2 Exclusion Criteria**

Subjects who meet one or more of the following criteria will not be considered eligible to participate in the clinical trial:

1. Any deviation from the normal range in biochemistry or haematology blood tests or in urine analysis that is considered to be clinically significant at the discretion of the

investigator. Values of Hb, WCC, platelet count, AST/ALT and creatinine should be in a normal range accordingly to the normal laboratory values.

2. Use of any investigational or non-registered drug, vaccine, or medical device other than the trial vaccine within 30 days prior to dosing of trial vaccine, or planned use during the trial period.
3. Administration of chronic (defined as more than 14 days) immunosuppressive drugs within six months of vaccination and required throughout the duration of the trial (for corticosteroids this means prednisolone or equivalent at  $\geq 0.5$  mg/kg/day).
4. Female of child bearing potential who intends to become pregnant during the trial.
5. Females who are pregnant, lactating, or of child bearing potential with a blood HCG positive result 24-48 hours at the screening period, or prior to every injection of RUTI®.
6. Any AIDS defining illness according to the CDC classification system for HIV infection (Appendix 17.1).
7. Presence of active (previously undiagnosed) TB or being on TB treatment.
8. Suspected or known current alcohol abuse (alcohol intake questionnaire, Appendix 17.2).
9. Suspected or known substance abuse.
10. Presence of any underlying disease, specifically autoimmune disease, asthma, angioedema, bleeding disorders, uncontrolled hypertension and diabetes, and any other disease that compromises the diagnosis and evaluation of response to the vaccine, excluding HIV.
11. Administration of immunoglobulins and/or any blood products within three months prior to the planned administration of the vaccine.
12. Any history of anaphylaxis in reaction to vaccination and/or other medication.
13. Investigator assessment of lack of understanding or willingness to participate and comply with all requirements of the trial protocol.
14. Any other finding which in the opinion of the investigator would significantly increase the risk of having an adverse outcome from participating in the trial.
15. Exclusion criteria relating to INH pre-treatment
  - Weight less than 40 kg.

- Known or suspected hypersensitivity to INH.
- Self reported chronic liver disease or symptoms suggesting active hepatitis (jaundice, nausea, vomiting, right upper quadrant pain, dark urine, pale stools).
- Alcohol use exceeding 28 units per week (men) or 21 units per week (women) (see alcohol intake questionnaire, Appendix 17.2).
- History of convulsions.
- History of psychosis.
- Peripheral neuropathy grade 2 or greater.
- Three months post-partum.
- Concomitant medication with phenytoin, carbamazepine; warfarin; theophylline; disulfiram; selective serotonin re-uptake inhibitor antidepressants (e.g. citalopram, fluoxetine, paroxetine, sertraline); oral ketoconazole or itraconazole.

16. Additional exclusion criterion for HIV negative groups:

- Any confirmed or suspected immunosuppressive or immunodeficient condition, including asplenia.

17. Additional exclusion criterion for HIV+ groups

- CD4 count < 350 cells/mL.

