## **5.2 Prohibitions and Restrictions. Medication(s)/Treatment(s) Permitted and not Permitted Before and/or During the Trial**

Potential subjects must be willing to adhere to the following prohibitions and restrictions during the course of the trial to be eligible for participation.

1. Must remain at the trial centre from at least 30 minutes after the vaccine administration.
2. Subjects will be advised not to donate blood during the trial and for at least two weeks after completion of the trial or to participate in an investigational drug trial for at least one month completion of the trial.
3. Must refrain from strenuous exercise of all types during the trial.
4. Subjects are strongly encouraged not to use alcohol and illicit substances during the entire trial.
5. Subjects are strongly encouraged not use medications or vaccines (excluding anti-retro viral treatment or users of anti-depressant drugs on stable dose) less than two weeks prior to baseline and during the trial.

If any concomitant medication is needed, it must be reported to the principal investigators and accepted by them. Principal investigators will be also responsible for treatment needed for AEs. Any treatment taken by subjects will be recorded in the CRF, as its dose and duration.

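### Exclusion 3 joins its two conditions with 'and', so its six-month window on immunosuppressive drugs has no effect of its own

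*Protocol*

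**What the plan says.** Section 4.2 of the Protocol opens its list with the rule "Subjects who meet one or more of the following criteria will not be considered eligible to participate in the clinical trial". Each item therefore works alone, and a subject missed by one may still be caught by another.

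Item 3, which defines chronic use as longer than 14 days, excludes subjects given "immunosuppressive drugs within six months of vaccination and required throughout the duration of the trial", and adds a dose threshold for corticosteroids. The two conditions are joined by 'and'.

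Item 2, on investigational products, is built differently. It excludes use "within 30 days prior to dosing of trial vaccine, or planned use during the trial period", so past use and planned use are alternatives. Item 11, on immunoglobulins and blood products, has a three-month look-back and no second condition.

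The other text that could bear on the same subjects is:

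- Exclusion 10: named diseases, including autoimmune disease and asthma, and "any other disease that compromises the diagnosis and evaluation of response to the vaccine, excluding HIV".
- Exclusion 14, which rests on judgement: "Any other finding which in the opinion of the investigator would significantly increase the risk of having an adverse outcome from participating in the trial".
- Exclusion 16, HIV-negative groups only: "Any confirmed or suspected immunosuppressive or immunodeficient condition, including asplenia".
- Inclusions 1, 3 and 9 (section 4.1): the subject is asymptomatic, has no clinically significant finding, and is positive on both the skin test and QuantiFERON.
- Section 5.2: "Subjects are strongly encouraged not use medications or vaccines" from two weeks before baseline and during the trial. Needed medication has to be reported to the principal investigators and accepted by them.

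**The concern.** A six-month look-back on chronic immunosuppressive drugs is there to keep recent drug-induced suppression out of the immune measurements. With 'and', it cannot do that for anyone who has stopped treatment, which is the group a look-back exists to catch.

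Immunogenicity is one of the two trial objectives (section 2). The secondary endpoints are mainly IFN-gamma responses (section 3.1), analysed by ANCOVA with the baseline value as covariate (section 9.3.2). A recently suppressed subject could contribute an unrepresentative baseline and an unrepresentative response in a cell of 12. Because that subject meets the criteria as written, entry would not be an eligibility deviation, and the Per Protocol definition in section 9.9 would not remove the subject on that ground.

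**Working it through.** The plan states no figure to reproduce, so the check is one of logic, with simple arithmetic on size.

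**Conditions in item 3**

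- A: chronic use (more than 14 days) within six months of vaccination.
- B: the drug is required throughout the trial.
- Literal rule: excluded if A and B.

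**Does the window do any work?** The trial runs from Day 0 to Day 84, and the injections are on Days 28 and 56 (sections 3.4 and 3.5). If B holds from Day 0, use before the first injection is 28 − 0 = 28 days. That is more than 14 days and lies within six months, so A holds as well. Hence B implies A, and 'A and B' reduces to B. Deleting the six-month clause would change nobody's status under item 3.

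**Cases under the literal rule**

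| Subject | A | B | Excluded by item 3? |
|---|---|---|---|
| On treatment before vaccination and needing it throughout | yes | yes | yes |
| Starts at Day 0 and needs it throughout | yes | yes | yes |
| Course of more than 14 days completed within six months before vaccination | yes | no | no |
| On treatment at entry, needed for only part of the trial | yes | no | no |
| No earlier use, course starting later in the trial | no (yes if the window also looks forward) | no | no |

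Changing 'and' to 'or' and nothing else would exclude the third and fourth rows. The fifth would remain unless the second condition also covered use planned for part of the trial, as item 2 does, or unless the window is read as looking forward.

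**Does other text set a drug-exposure rule?** Exclusion 10 turns on disease. Exclusion 14 turns on the investigator's view of risk, not on immune response. Exclusion 16 turns on a condition, in HIV-negative subjects only. Inclusions 1 and 3 turn on symptoms and clinical findings. Inclusion 9 requires T-cell reactivity, but section 5.1 places those tests at a pre-screen visit and makes a repeat only a possibility when they are more than four months old, so a course could fall after them. Section 5.2 discourages medication and gives the investigators acceptance. None of these sets a look-back for immunosuppressive drugs.

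**Size**

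- One subject in a dose-by-HIV cell: 1/12 = 8.3%.
- One subject in a dose arm pooled over HIV status: 1/(12 + 12) = 1/24 = 4.2%.
- The documents give no rate of recent immunosuppressive courses. If it were 1% to 3% before the other criteria act (an assumption), 0.01 × 96 = 0.96 to 0.03 × 96 = 2.88, or about 1 to 3 of 96 subjects. The other criteria would lower this.

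**The case against.** The best defence is that 'and' may list two separate grounds, recent use and continuing need. A reading that empties a stated window is weak evidence of what was intended. That is fair as to intent, but the text does not say so, item 2 shows how the same list expresses alternatives, and sites could apply item 3 differently.

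The second defence is that other criteria leave only a small residue. Autoimmune disease and asthma are plausible reasons for a long corticosteroid course, and exclusion 10 names both, in both HIV strata. A markedly suppressed subject is also less likely to pass inclusion 9. This stands in part. The accurate statement is that such a subject is not excluded by item 3, which is weaker than saying that the subject is eligible.

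A reader might go further in four ways that the documents do not support:

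- That the washout is in effect zero days. A subject whose course ended just before Visit 1 is still about four weeks off the drug at the Day 28 injection.
- That the gap is wider in HIV-positive subjects because they have no counterpart to exclusion 16. That item concerns a condition. If it does not catch drug exposure, it does not narrow the gap in HIV-negative subjects either. It could hardly apply to HIV-positive subjects, whose own rule is the CD4 threshold. Section 9.3.2 specifies no formal comparison by HIV status.
- That this is a safety defect. Section 3.4 describes a detoxified, pasteurised product, the trial enrols HIV-positive subjects by design, and nothing in the protocol shows a hazard after stopped treatment.
- That it biases the dose comparison. Randomisation follows eligibility and the INH month, so affected subjects fall across arms by chance.

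**Conclusion.** The concern holds as a wording defect. Taken literally, item 3 excludes only subjects who need chronic immunosuppressive drugs throughout the trial, and its six-month window adds nothing. Completed courses and part-trial courses are left to disease-based or discretionary criteria that do not address drug exposure.

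The consequence is modest: possible added noise or dilution in secondary endpoints of an exploratory trial, at 8.3% of a cell or 4.2% of a pooled arm for each affected subject. How many would enter cannot be derived from the documents. No stated figure changes. The conclusion rests on the literal reading of 'and'. If the sponsor meant two separate grounds, the point becomes one of ambiguity, and the same correction settles it.

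**What to change.** Reword item 3 so that either ground is enough, on the pattern of item 2: chronic use within six months of vaccination, *or* use required or planned during the trial. The second ground should not depend on need throughout the trial; otherwise part-trial courses remain outside it. The protocol's own six-month window, 14-day definition and corticosteroid threshold stay unchanged.

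The cost is a short amendment and a few more screen failures. No new procedure is needed, because the section 5.1 schedule already collects clinical history and concomitant medication at screening.

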### **Dosage and Administration**

A total of three doses of RUTI® vaccine will be tested: 5, 25 and 50µg of FCMtb, chosen from the Phase I clinical trial experience in terms of tolerability and polyantigenic immune response.

A single dose of the vaccine or placebo (0.3 mL) will be administered twice to the subjects, 28 days apart (on days 28 and 56), by subcutaneous route, after one-month of INH pre-treatment. Sites of injection will be alternated (i.e., the injection should be given subcutaneously in the deltoid muscle area [right or left] that is opposite to the previous injection site). Both the injection site and the opposite deltoid muscle should be evaluated during the course of the trial. The exact date and times of each trial drug administration will be recorded in the CRF together with the side of the injection (right or left deltoid muscle).

Subjects will be followed-up for safety and immunogenicity parameters until the end of the trial

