## 5. TREATMENT OF SUBJECTS

### 5.1 Treatment to be Administered (Product, Dose, Dosing Schedule, Route of Administration, Treatment Period, Follow-up Period for Subjects)

Four weeks of INH pre-treatment will be administered to all subjects (subjects will keep a diary card to ensure INH treatment compliance), prior to randomization to receive either placebo or RUTI® s.c. twice, on 28th and 56th day (28 days apart). The criterion to be met prior to randomisation is to complete one month of INH (assessed by self reported adherence to INH) and no evidence of active TB prior to vaccination.

The monitoring will include complete physical examinations, laboratory sampling, blood extractions to perform safety and immunogenic tests, HIV+ status evaluation (CD4 counts) when required, and INH pre-treatment surveillance by self-reported adherence to INH. All the patients will be tightly followed-up, and an active TB surveillance will be done (see Section 8). A subject will be considered to have completed the trial if he or she completed all required assessments at the end of the follow-up period.

All the planned activities of the trial are shown in the figure below ([Figure 19](#)). As indicated in this figure, the TST, Quantiferon Gold and HIV tests, and chest X-ray will be done at a pre-screen visit. The HIV test will be repeated at screening if the results were negative at the pre-screen visit. In the event that the pre-screen tests were performed longer than 4 months before the screening visit, it may be required to repeat the tests at screening. The chest X-ray may however be repeated at screening at the discretion of the investigator. As part of the monitoring plan there have been scheduled:

- the activities designed to screen the population for the trial
- the Safety measures
- Immunogenicity measures
- Other important activities for the trial are marked: Vaccine/Placebo Inoculation and decision to do it; INH pre-treatment and participant reports to verify its compliance; and active TB surveillance.

All the relevant activities of the subjects will be reported on Case Report Forms (CRF).

| Phase II: Safety and Immunogenicity of INH 1 month plus RUTI |                     |        |   |    |              |          |               |    |    |    |              |          |               |    |    |    |

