|--------------------------------------------------------------|---------------------|--------|---|----|--------------|----------|---------------|----|----|----|--------------|----------|---------------|----|----|----|
|                                                              | Study design        |        |   |    |              |          |               |    |    |    |              |          |               |    |    |    |
|                                                              |                     | INH Tt |   |    | Pre 1st dose | 1st dose | Post 1st dose |    |    |    | Pre 2nd dose | 2nd dose | Post 2nd dose |    |    |    |
|                                                              | HIV+ & HIV-subjects |        |   |    |              |          |               |    |    |    |              |          |               |    |    |    |
| Visit                                                        | S                   | 1      | 2 | 3  | 4            |          | 5             | 6  | 7  | 8  | 9            |          | 10            | 11 | 12 | 13 |
| Day                                                          | .-28/-1             | 0      | 7 | 21 | 28           |          | 29            | 31 | 35 | 49 | 56           |          | 57            | 59 | 63 | 84 |
| Week                                                         | .-4/-1              | 1      | 2 | 4  | 5            |          |               |    | 6  | 8  | 9            |          |               |    | 10 | 13 |
| Information to the patient, Informed consent                 | X                   |        |   |    |              |          |               |    |    |    |              |          |               |    |    |    |
| Clinical History                                             | X                   |        |   |    |              |          |               |    |    |    |              |          |               |    |    |    |
| Inclusion/exclusión Criteria                                 | X                   | X      |   |    |              |          |               |    |    |    |              |          |               |    |    |    |
| Vaccine inoculation Decision                                 |                     |        |   | X  |              |          |               |    | X  |    |              |          |               |    |    |    |

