| Vital Constants                                              | X                   | X      | X | X  | X            |          | X             | X  | X  | X  | X            |          | X             | X  | X  | X  |
| Physical examination                                         | X                   | X      | X | X  | X            |          | X             | X  | X  | X  | X            |          | X             | X  | X  | X  |
| Pregnancy test                                               | X                   |        |   |    | X            |          |               |    |    | X  |              |          |               |    |    | X  |
| Serology (HIV, VHB, VHC)                         | X                   |        |   |    |              |          |               |    |    |    |              |          |               |    |    |    |
| TST + Quantiferon                                | X                   |        |   |    |              |          |               |    |    |    |              |          |               |    |    |    |
| Chest X-Ray                                      | X                   |        |   |    |              |          |               |    |    |    |              |          |               |    |    |    |
| Chest CT                                                     |                     |        |   |    | X            |          |               |    |    |    |              |          |               |    |    | X  |
| ECG                                                          | X                   |        |   |    |              |          |               |    | X  |    |              |          |               |    |    | X  |
| Concomitant medication                                       | X                   | X      | X | X  | X            |          | X             | X  | X  | X  | X            |          | X             | X  | X  | X  |
| General Laboratory sampling                                  | X                   |        |   | X  | X            |          |               |    | X  | X  | X            |          |               |    | X  | X  |
| Immunogenicity sampling                                      |                     | X      |   |    | X            |          |               |    | X  |    | X            |          |               |    | X  |    |

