**Vital Signs**

Blood pressure (systolic and diastolic), pulse, respiratory rate and body temperature will be assessed for 5 minutes post vaccination.

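### Exclusion criterion 5 gives a garbled 24-48 hour window for the HCG check before injections, and Figure 19 schedules no pregnancy test between Day 49 and the Day 56 dose

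*Protocol*

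**What the plan says.** Section 4.2, item 5, disqualifies women who are pregnant or lactating, and women of child-bearing potential with a "blood HCG positive result 24-48 hours at the screening period, or prior to every injection of RUTI". The dosing text in Section 3.4 fixes the two injections as "28 days apart (on days 28 and 56".

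Figure 19 in Section 5.1 is the activity schedule. Its row "Pregnancy test" is marked at screening, Visit 4 (Day 28), Visit 8 (Day 49) and Visit 13 (Day 84). Visit 9 (Day 56) is blank in that row. Its row "Vaccine inoculation Decision" is marked at Visit 3 (Day 21) and Visit 7 (Day 35) only.

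Section 5.1 also sets a condition for randomisation: "The criterion to be met prior to randomisation is to complete one month of INH", judged by self-report, together with no evidence of active TB before vaccination. Section 3.3 allows the inoculations once safety is assured. Section 3.2 refers the decision-making mechanism to Figure 18, which is not shown in the text available here.

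Section 7.1 says that vital signs "will be assessed for 5 minutes post vaccination". In Figure 19 they are marked at every numbered visit, but not in the two dose columns.

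**The concern.** Section 5.1 presents Figure 19 as holding all planned activities, so sites will work from it. A site that follows the chart exactly has no pregnancy result for dose 2 more recent than Day 49. If criterion 5 means a short window before each injection, following the schedule breaches the eligibility text at dose 2 for every woman of child-bearing potential. If it means something else, investigators cannot tell from the wording what window they must meet.

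The decision row raises a related question. Both marks fall before results or conditions that the text attaches to randomisation or injection, and no later decision is marked. A reader cannot tell whether the decision taken at those visits is a provisional check or the final go-ahead.

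**Working it through.** **Reading the chart.** Figure 19 has 16 columns after the row label: screening, Visits 1-4, dose 1, Visits 5-9, dose 2, Visits 10-13 (1 + 4 + 1 + 5 + 1 + 4 = 16). Each row used here has 16 cells. Three checks suggest that the cells have not shifted:

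- The inoculation marks fall in the two dose columns.
- The chest CT marks fall on Day 28 and Day 84. Section 7.1 places the CT before the first inoculation and four weeks after the second, and 84 - 56 = 28 days.
- INH provision falls on Days 0, 7 and 21, inside the four-week INH period.

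**The plan's own interval.** Day 56 - Day 28 = 28 days between injections, as stated.

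**Pregnancy test against injection.**

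| Injection | Last scheduled test | Gap | Against 24-48 h before injection |
|---|---|---|---|
| Dose 1, Day 28 | Day 28 | 28 - 28 = 0 days | Same day, so not 24-48 h before |
| Dose 2, Day 56 | Day 49 | 56 - 49 = 7 days = 7 × 24 = 168 h | 168 - 48 = 120 h = 5 days outside the 48 h limit |

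**The two readings of item 5.**

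- *Window before each injection.* Figure 19 does not meet it at dose 2, by 5 days. Read strictly, the same-day test at dose 1 does not meet it either.
- *Window at screening only.* The Day 49 test is still prior to dose 2, so the passages do not conflict. The remaining faults are that a 24-48 hour window attached to a screening period has no clear meaning, and that no window is then given for the injections.

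The first reading is the more natural, because a window in hours needs an event to count from and an injection is such an event. The wording does not settle it.

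**Decision marks against the conditions in the text.**

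| Decision | Condition | Gap |
|---|---|---|
| Day 21 (dose 1) | One month of INH completed, Day 28 (Section 5.1, before randomisation) | 28 - 21 = 7 days before |
| Day 21 (dose 1) | HCG test on Day 28 (Section 4.2, item 5) | 28 - 21 = 7 days before |
| Day 35 (dose 2) | HCG test on Day 49 (Section 4.2, item 5) | 49 - 35 = 14 days before |
| Day 35 (dose 2) | Injection on Day 56 | 56 - 35 = 21 days before |

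**The case against.** The strongest objection on the pregnancy test is that the hours sit next to the screening period in the sentence. On that reading a Day 49 test satisfies the rest of the criterion. This stands as a possible reading, so the conflict is conditional. It does not rescue the wording.

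On the decisions, a reader might infer that they are taken before the data they rest on, such as the Day 28 CT and the later laboratory draws. The documents do not support that:

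- The readable text never lists the inputs to the decision, and the mechanism is referred to Figure 18.
- The CT is not stated as a condition for vaccination. Section 7.1 describes it as a measure of change in hilar lymph node size.
- Both decision visits have a laboratory draw of their own in the row "General Laboratory sampling", which fits a decision based on that visit's data.
- INH completion is a condition for randomisation, and nothing equates the Day 21 mark with randomisation.
- Examination, vital signs, adverse event questioning and local inspection follow at Visits 8 and 9. The investigator (Section 4.3) and the DSMC (Section 3.6) can stop a subject for safety reasons.

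What is left is that two explicit conditions, INH completion and the HCG result, fall after the marks, and that the readable text does not say whether the decisions are provisional.

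A reader might also infer that vital signs after vaccination will not be collected. An unmarked dose column does not cancel the explicit instruction in Section 7.1, and vital signs are also marked on the day after each dose (Days 29 and 57). This is an editorial gap.

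Finally, a reader might infer losses from the Per Protocol population, or an effect on all 96 subjects. Section 9.9 leaves the detailed exclusion reasons to the SAP and the blind data review, and it defines a separate Safety Population for the primary safety endpoint. Neither consequence can be shown from the protocol.

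**Conclusion.** The point holds in a limited form. Criterion 5 is ambiguous, and Figure 19 has no pregnancy test between Day 49 and the Day 56 injection. If the 24-48 hours applies before each injection, the last scheduled test before dose 2 is 168 h earlier, 5 days beyond the 48 h limit, and the dose 1 test is same-day. If the hours apply to screening only, there is no conflict, only an unclear criterion. The point concerns women of child-bearing potential, whose number the protocol does not give.

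As a secondary point, the Day 21 and Day 35 decision marks precede INH completion and the HCG results, and their status is not stated in the readable text.

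This rests on the column positions in Figure 19 as extracted, which agree with the text wherever they could be checked, and on Figure 18 being unavailable. It is worth correcting because it is a safety check and the correction is small. It does not bear on the statistical analysis.

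**What to change.** 1. Reword Section 4.2, item 5, so that it is clear which event the 24-48 hours is counted from, and whether it applies at screening, before each injection, or both.
2. Reconcile the reworded criterion with the pregnancy-test row of Figure 19 for both injections, using visits already scheduled.
3. State in Section 5.1 whether the decisions marked on Days 21 and 35 are provisional pending the conditions that fall after them. If Figure 18 already says so, refer to it there.
4. As an editorial alignment, mark the post-vaccination vital signs of Section 7.1 in the two dose columns of Figure 19.

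Which timing is right for the test and the decisions is for the clinical team. The cost is a wording change and a correction to the flow chart and CRF. At most, an existing check moves between visits already in the schedule.
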